**(2) Secondary endpoints:**

- Food restriction scale score at 3, 6, 12 months after operation

- Meal amount (total calories, nutrient amount)

- Body component (body weight, body mass index, muscle mass, body fat percentage)

- Nutritional outcomes (hemoglobin, protein, albumin, cholesterol)

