**(4) Drop-out criteria**

1. Patients who have not undergone distal gastrectomy or total gastrectomy

1. The pathology test result is stage II or higher after gastrectomy
2. Patients who need adjuvant chemotherapy after gastrectomy

4. The hospital stay exceeds 3 weeks due to complications

5. Patients request withdrawal of participation

6. Patients having difficulty in collecting data suitable for the purpose of the study because they have not visited at all 1, 3, 6, and 12 months

1. **Study diagram**

|  | Informed consent | |  |
| --- | --- | --- | --- |
|  |  |  |  |
|  | Screening | |  |
|  |  |  |  |
|  | Gastrectomy | |  |
|  |  |  |  |
|  | Follow-up at 1, 3, 6, 12 months after operation | |  |

| **Data** | **Preop** | **Op** | **POD5** | **POD1m** | **POD3m** | **POD6m** | **POD12m** |
| --- | --- | --- | --- | --- | --- | --- | --- |
| age, sex, height, past medical history, smoking, alcohol, concomitant medications | O |  |  |  |  |  |  |
| operating day, operation method |  | O |  |  |  |  |  |
| pathological results of gastric cancer, postoperative complications |  |  |  | O |  |  |  |
| body weight | O |  | O | O | O | O | O |
| body component such as muscle mass measured with a body composition analyzer | O |  |  | O | O | O | O |
| EORTC QLQ C30, STO22 | O* |  |  | O | O | O | O |
| Hb, Protein, Albumin, Cholesterol | O |  | O |  | O | O | O |

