**(5) Outcome parameters**

- Comparison of food restriction scale score of EORTC QLQ C30, STO22:

Whether there is a significant difference in the mean value is evaluated by the p-value of the t-test. Since the 1st month questionnaire is the primary endpoint, it is evaluated individually and the significance of the mixed model's p-value is evaluated to see if there are overall differences in the values ​​measured several times.

- Inbody values ​​such as meal volume, BMI, muscle mass, and blood tests were compared with the average value at 3 months, and the significance was evaluated by the p-value of the mixed model to see if there was a difference overall.

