**(2) Schedule**

| List | Screening | Follow-up | Close |
| --- | --- | --- | --- |
| Check inclusion/exclusion criteria | X |  |  |
| Demography | X |  |  |
| Diagnosis, pathological results, complications | X | X |  |
| Body component |  | X |  |
| QoL questionnaire |  | X |  |
| Nutritional parameters |  | X |  |
| Use of smartphone app. |  | X |  |
| Report |  |  | X |

(3) **Study period**

- Research participation period: One year after gastrectomy for early gastric cancer

- Data collection period: IRB approval day – 2021. 12. 31

- Overall study period: IRB approval day – 2022. 6. 30.

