**9. Statistical Methods**

(1) **Randomization**

- Randomization generally performs permutated mixed block randomization, and is generated in a 1:1 ratio using 2 and 4 mixed block blocks. Using the nQuery Program, a randomly assigned table is created according to the stratification factor and notified through a web-based clinical research management system.

- Stratification factors: extent of gastrectomy (distal vs. total gastrectomy)

(2) **Statistical analyses**

- Patient's clinical characteristics are expressed as mean ± standard deviation or ratio using descriptive statistics.

- Significance was evaluated by t-test for continuous variables and Chi-square test for discontinuous variables.

- For the values ​​repeatedly measured at time intervals, the difference between the two groups was compared using a mixed effect model.

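### The 3-month comparison of body and blood endpoints makes no stated use of the scheduled pre-operative values, and the section 8(2) schedule leaves those measurements out

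*Protocol*

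**What the plan says.** **Endpoints.** Section 2(2) lists the secondary variables by name, including "Body component (body weight, body mass index, muscle mass, body fat percentage") and "Nutritional outcomes (hemoglobin, protein, albumin, cholesterol"). For these it gives no time point and no summary measure. Section 7(2) compares them between arms at 1, 3, 6 and 12 months.

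**Analysis.** Section 7(5) fixes a time point: meal volume, BMI, "muscle mass, and blood tests were compared with the average value at 3 months". The same sentence adds a second analysis, in which "the significance was evaluated by the p-value of the mixed model to see if there was a difference overall". Section 9(2) gives the general methods: "Significance was evaluated by t-test for continuous variables and Chi-square test for discontinuous variables", and for repeated values "the difference between the two groups was compared using a mixed effect model". Neither section mentions change from, or adjustment for, the pre-operative value.

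**Measurement.** There are two schedules. The data table under the study diagram, which follows the drop-out criteria in section 4, marks the pre-operative column for body weight, body composition, both questionnaires and the four blood tests. The body-composition row begins "body component such as muscle mass measured with a body composition analyzer | O", where the mark is the pre-operative one. The section 8(2) table has three columns (Screening, Follow-up, Close). Its row reads "Body component | | X", so Screening is blank and only Follow-up is marked. The rows for the quality-of-life questionnaire and nutritional parameters follow the same pattern.

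**The concern.** Weight, BMI, muscle mass and, to a lesser degree, blood values differ between patients before any operation, and much of that difference persists afterwards. A plain comparison of 3-month means carries all of this stable variation in its error term. The pre-operative value can remove part of it, and it is a legitimate covariate: patients are randomised while awaiting gastrectomy and coaching starts only after discharge, so the allocated programme cannot have influenced it.

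Two things are at stake. The first is power for the nutritional secondary endpoints, for which the trial was not sized. The second is the baseline itself. If study staff work from the section 8(2) table, a body-composition reading may not be taken before surgery, and it cannot be taken afterwards.

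**Working it through.** **The plan's own figure.** Section 6(2) gives means of 30 and 35, SD 10, alpha 0.05 and power 80%. With n per arm = 2 × (1.960 + 0.842)² × (10/5)², the result is 63; a t-based calculation gives 64. The stated 65 is reproduced within two patients. Of the 90 randomised per arm, 90 × 0.7 = 63 remain after the 30% allowance. That figure concerns the primary endpoint only. It is used here to set the number evaluable.

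**Inputs for the secondary endpoints.**
- From the protocol: 63 evaluable per arm, two-sided alpha 0.05 (the protocol does not state sidedness, but two-sided reproduces its figure), power 80%.
- Assumed: the correlation r between the pre-operative and 3-month value, varied from 0.3 to 0.9, and equal SDs at the two times. The protocol gives neither.

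**Formulas**, in units of the SD of the 3-month value:
- Unadjusted 3-month mean: (1.960 + 0.842) × √(2/63) = 2.802 × 0.178 = 0.50
- Baseline as covariate: 0.499 × √(1 − r²)
- Change from baseline: 0.499 × √(2(1 − r))

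For example, at r = 0.8 the covariate analysis gives 0.499 × √0.36 = 0.30, and change gives 0.499 × √0.40 = 0.32.

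| r | Unadjusted | Covariate | Change |
|---|---|---|---|
| 0.3 | 0.50 | 0.48 | 0.59 |
| 0.5 | 0.50 | 0.43 | 0.50 |
| 0.7 | 0.50 | 0.36 | 0.39 |
| 0.8 | 0.50 | 0.30 | 0.32 |
| 0.9 | 0.50 | 0.22 | 0.22 |

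**Power for a true difference of 0.3 SD.** Unadjusted: 39%. With the covariate: 42%, 49%, 66%, 80% and 97% at r = 0.3, 0.5, 0.7, 0.8 and 0.9. With change: 30%, 39%, 59%, 76% and 96%.

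**Patients per arm for 80% power at 0.3 SD.** Unadjusted: 175. With the covariate: 159, 131, 89, 63 and 34 at the same correlations. With change at r = 0.3: 245, which is more than the unadjusted comparison needs.

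**The two schedules side by side.** The data table has a pre-operative mark on the body-composition, questionnaire and blood-test rows. The section 8(2) table has no Screening mark on the corresponding rows. It does use the Screening column elsewhere, and it marks diagnosis, pathology and complications at both Screening and Follow-up. Its blanks therefore read as *not measured*, and the two tables disagree.

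**The case against.** The strongest reply is that nothing is invalid. Allocation is randomised 1:1, so the difference in 3-month means is unbiased, and the t-test's standard error already allows for chance imbalance at baseline. This stands. A reader might infer that an absolute comparison hides the nutritional effect, or favours the arm with heavier patients; the documents do not support that. What is lost is precision.

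Second, section 7(5) also names a mixed model. The pre-operative value could enter it, and model terms are commonly left to a statistical analysis plan, which is not at hand. This also stands: it cannot be said that the baseline values will go unused. But that model addresses an overall difference, whereas the separate 3-month comparison is already written and, read with section 9(2), has no covariate.

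Third, a reader might want every endpoint redefined as loss from baseline. The table above argues against that. Change is less precise than the raw value when r is below 0.5, which is possible for some blood values. The covariate analysis was no worse than either alternative at any correlation tried.

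Fourth, the section 8(2) table is a summary in a single-centre study, and the more detailed table does schedule the baseline. Section 12(2) also provides for a search of medical records, from which weight and blood values might be recovered. It would therefore go too far to say that the baseline is not collected or is lost. Body weight is a particular case: it has no row of its own in section 8(2), although section 2(2) counts it under body component, and the sentence in section 7(5) does not name it. The contradiction between the tables remains, and it matters most for the body-composition readings.

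**Conclusion.** The point holds as an inexpensive improvement to secondary endpoints. The 3-month comparison is stated on absolute means with no use of a baseline that the trial plans to collect, and one of the two schedules omits that baseline.

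The size depends on r. Relative to the unadjusted analysis, the detectable difference falls by about 5% at r = 0.3 (0.499 to 0.476), 40% at r = 0.8 (0.499 to 0.300) and 56% at r = 0.9 (0.499 to 0.218). High correlations are plausible for weight, BMI and muscle mass, but they are an assumption here, as is equality of the SDs. The gain for blood values may be small. The documents do not support a reading of bias, of an unusable comparison, or of any effect on the primary endpoint or the sample size.

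**What to change.** 1. In section 7(5), state that the 3-month comparison and the mixed model for body weight, BMI, muscle mass, body fat percentage, hemoglobin, protein, albumin and cholesterol include the pre-operative value of the same variable as a covariate. In the mixed model it should not also appear as an outcome time point. Meal volume cannot be treated this way, because the data table schedules no pre-operative value for it.
2. Report percent loss of weight and of muscle mass from the pre-operative value descriptively by arm, since clinicians will want those figures.
3. Reconcile section 8(2) with the data table, so that both show the pre-operative measurement of body component, quality-of-life questionnaire and nutritional parameters.
4. State how patients without a pre-operative value are handled, so that they are not silently dropped from the adjusted analysis.

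The cost is wording, plus the rule in item 4. The data table already schedules the measurements, and one extra covariate uses one degree of freedom with about 126 patients.

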**8. Study method**

**(1) Study method**

- Patients who are scheduled to undergo gastrectomy for stage 1 gastric cancer are randomly assigned either to the mHealth group or the face-to-face counseling group. Patients in the mHealth group (N=90) will use mobile application for 3 months after discharge and those who in the face-to-face counseling group (N=90) will receive general nutrition counseling at 1 month and 3 months after gastrectomy.

[figure not shown]

- Patients will receives nutritional counseling at 1 month (30 days) and 3 months (90 days) after gastrectomy by randomization. The allowable date of visit to the hospital is 1 month before and after 1, 3, 6, 12 months after surgery. If the patient does not visit the hospital and cannot be contacted, the study coordinator attempts to contact the hospital by phone or text once a week for a month. Subject will be eliminated from the study if he did not visit the hospital at all the follow-up period.

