| **Study method** | - Patients who are scheduled to undergo gastrectomy for stage 1 gastric cancer are randomly assigned either to the mHealth group or the face-to-face counseling group. Patients in the mHealth group (N=90) will use mobile application for 3 months after discharge and those who in the face-to-face counseling group (N=90) will receive general nutrition counseling at 1 month and 3 months after gastrectomy.  - QOL, body component, and nutritional outcomes will be compared between the two groups.  - When obtaining the consent form, the mHealth group will be provided with a simple noom instruction manual and a noom meal record guide, and will be informed of how to use it.  - In addition, individual coaching will be given through articles and messengers on how to manage post-gastrectomy such as weight, diet, and exercise on the mobile app for 3 months from the discharge date.  - Survey response on quality of life at outpatient visits 1, 3, 6, 12 months after surgery  [figure not shown]  * The allowable date of visit at 1, 3, 6, and 12 months after surgery is 1 month before and after. | | | | |
| **Intervention method** | **- mHealth group:** After being discharged from hospital, patients will receive coaching using a smartphone app for 3 months. When the patient is discharged from the hospital, he downloads the Noom app on his or her mobile phone, registers, and then uses the Noom program. In addition, a personal coach is assigned to provide appropriate coaching to the patient on the app.  **-Face-to-Face group:**　Patients will receive individual nutrition counseling from a clinical nutritionist at the hospital at 1 month and 3 months after surgery. | | | | |
| **Evaluation** | Between the mHealth and face-to-face groups  - Comparison of scores of EORTC QLQ-C30 and STO22 at 1, 3, 6, and 12 months postoperatively.  - Comparison of meal amount at 1, 3, 6, and 12 months postoperatively.  - Comparison of body component (BMI, muscle mass, etc) at 1, 3, 6, and 12 months postoperatively.  - Comparison of nutritional outcomes (hemoglobin, albumin, protein, cholesterol) at 1, 3, 6, and 12 months postoperatively | | | | |

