**(2) Dietary adaptation of the patient**

- Patients receive nutritional counseling during the hospitalization period, but when they return to their daily life after discharge, there is no separate education on how to eat and how to adjust, resulting in various trials and errors.

- In particular, after being diagnosed as a cancer patient, there are cases where people around us hear unverified stories and eat mainly with certain foods, or they may not be able to consume enough nutrition due to restrictions on certain foods.

- They are also not well aware of postgastrectomy syndrome, so they constantly experience discomfort after eating.

- This postgastrectomy syndrome is most severe in the early postoperative period and gradually relieves after dietary adaptation.

(3) **Diet management using a smartphone app**

[figure not shown]
- Currently, for weight loss, a smartphone app (Noom) is being used that keeps a daily meal diary, calculates meal calories, and provides 1:1 customized coaching service.

- Noom not only makes it easy for users to enter the food eaten during the day based on the food database, but also helps the coach in charge check daily to keep the dietary control.

- If Noom is used in the process of dietary adaptation after surgery for gastric cancer patients, it is expected that balanced nutritional intake will be achieved through appropriate dietary disorders. In addition, by providing information on gastrectomy syndrome, it is possible to reduce and prevent gastrectomy syndrome.

- Also, as Noom actively encourages exercise therapy, the patient is motivated for proper exercise.

- This is expected to reduce the patient's symptoms and improve the quality of life.

(4) **Previous literature review**

- In the past literature, the results that weight control and metabolic syndrome control were significantly improved when using a smartphone app were published in several papers.

- There have also been studies showing that breast cancer survivors, which are highly related to obesity, lose weight, increase vegetable intake, and increase exercise volume when nutritional control using a smartphone app is used.

- Regarding stomach cancer, a study on improving lung capacity with a mobile self-monitoring tool has been published, and studies related to nutrition or diet have only been introduced with protocols so far.

[figure not shown]

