**2. Study Objectives**

**(1) Primary endpoint:**

- Analysis of the effect of using a smartphone app-based human coaching program on the patient's symptoms and quality of life in patients who underwent gastrectomy for stage 1 gastric cancer

- Comparison of food restriction scale scores of EORTC QLQ C30 and STO22 at 1 month after surgery between the patients who used smartphone app and those who received nutrition counseling

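### With a 1-month primary endpoint, the control arm's first scheduled counselling session falls at the visit where the outcome is measured, so the contrast is app coaching versus no scheduled post-discharge counselling

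*Protocol*

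**What the plan says.** **App arm.** The synopsis (Intervention method) states: "After being discharged from hospital, patients will receive coaching using a smartphone app for 3 months".

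**Control arm.** The same row states: "Patients will receive individual nutrition counseling from a clinical nutritionist at the hospital at 1 month and 3 months after surgery". Section 8(1) says that these patients "will receive general nutrition counseling at 1 month and 3 months after gastrectomy", and gives the dates in days: "nutritional counseling at 1 month (30 days) and 3 months (90 days) after gastrectomy by randomization". No control session is listed between discharge and day 30.

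**Assessment.** The synopsis (Study method) has the quality-of-life survey answered at the outpatient visits at 1, 3, 6 and 12 months. The data table under the study diagram agrees and adds a preoperative form.

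**Primary endpoint.** Section 2(1) names "Comparison of food restriction scale scores of EORTC QLQ C30 and STO22 at 1 month after surgery", and describes the comparison as "between the patients who used smartphone app and those who received nutrition counseling". Section 7(5) gives the reason for a separate test: "Since the 1st month questionnaire is the primary endpoint". The synopsis (Purpose) instead puts the primary comparison of the STO22 scale at 3 months.

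**Care outside the randomised arms.** Section 1(2) says that patients are counselled on nutrition while in hospital, but that "when they return to their daily life after discharge, there is no separate education on how to eat".

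**The concern.** The two interventions start at different times, and the primary measurement under sections 2(1) and 7(5) falls where one has been running for some time and the other is only about to begin. The comparator named in section 2(1) is nutrition counselling that patients have received. At the 1-month visit the face-to-face arm has had no time to act on any outpatient session.

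What is at stake is the meaning of the main result. A significant 1-month difference, read through the arm names and the wording of section 2(1), would be taken as evidence that the app does better than face-to-face counselling. The 1-month data cannot carry that claim. Neither a larger sample nor a different model would change this, because the limitation lies in the timing of measurement.

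**Working it through.** **Step 1. Exposure before each visit, on nominal dates.** Control sessions are at day 30 and day 90. I assume the questionnaire and the session share a visit, and that the scheduled counselling belongs to the control arm only.

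| Visit | Control sessions completed before the visit | App coaching |
|---|---|---|
| 1 month | 0 of 2 | from discharge to about day 30 |
| 3 months | 1 of 2 | most of its 3 months |
| 6 months | 2 of 2 | finished |

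For app exposure at 1 month, let L be the postoperative day of discharge, so exposure is 30 − L days. A stay beyond 3 weeks because of complications is a drop-out criterion, so I take L = 21 as the upper end: 30 − 21 = 9 days. If discharge were as early as day 5, the day of a scheduled in-hospital measurement (my assumption; the protocol gives no discharge day), exposure would be 30 − 5 = 25 days. Across this range the app arm has been coached and the control arm has had no earlier session.

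**Step 2. Order within the visit.** The protocol does not say whether the questionnaire or the counselling comes first. If counselling came first on the same day, the control arm would have had one session, but only hours earlier, and it could hardly have changed eating. The visit window of one month either side lets the 1-month visit fall between 0 and 2 months after surgery. The contrast would change only if counselling were given near day 30 and the questionnaire clearly later, and the text describes no such separation.

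**Step 3. The sample size is tied to the 1-month contrast.** Inputs from section 6(2): means 30 and 35, SD 10, alpha 0.05 (taken as two-sided), power 80%.

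n per group = 2 × (1.960 + 0.842)² × 10² / 5² ≈ 62.8, so 63. The t-test version gives 64. The stated 65 is reproduced to within two patients. With 30% drop-out, 63 / 0.7 = 90 per group, the stated enrolment. The arithmetic is sound for a 1-month difference of 5 points, and the protocol gives no corresponding 3-month difference or SD.

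**Step 4. What a move to 3 months would need.** The pilot medians for eating restriction were 30.0 (IQR 13.3 to 56.7) at 1 month and 20.0 (IQR 3.3 to 26.7) at 3 months, so the 1-month means cannot simply be carried over. As a rough guide, assuming normality, SD ≈ IQR width / 1.349:

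- 3 months: (26.7 − 3.3) / 1.349 = 17.3. A 5-point difference would need 189 per group; 63 evaluable would give about 37% power.
- 1 month: (56.7 − 13.3) / 1.349 = 32.2. The same difference would need 650 per group; 63 would give about 14% power.

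These come from at most 14 pilot completers (20 − 6) and skewed scores. The pilot spread exceeds the assumed SD of 10 at both times, so this is no argument for keeping 1 month. It does show that the sample-size basis has to be restated if 3 months is chosen.

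**The case against.** The best counter-argument is that the early measurement may be intended. Section 1(2) says that post-gastrectomy symptoms are worst in the early postoperative period, and the synopsis presents the app as allowing coaching at the right moment. Coaching from discharge versus hospital sessions that start at 1 month is a legitimate comparison of two care strategies, and randomisation protects it at 1 month. The wording in section 2(1) could also be read as merely naming the arms. This stands to the extent that a 1-month primary is not invalid. But no section states the contrast in those terms, and section 2(1) describes counselling received.

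Three stronger readings are tempting, and the documents do not support them.

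- *A positive result would show only that coaching beats nothing.* Section 1(2) describes inpatient counselling, and nothing withholds it from either arm. What is absent is scheduled counselling after discharge.
- *Control patients are stated to have had none of their two sessions.* That is the likeliest reading of the schedule, not a stated fact. The order within the visit is not fixed, and the study-method figures are not available to check.
- *The trial cannot answer its own question.* Under the synopsis's 3-month primary, one control session would normally precede the measurement and the problem largely disappears. Under 1 month, the trial answers a narrower question than the one worded.

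**Conclusion.** The point holds, conditional on the 1-month primary of sections 2(1) and 7(5). On the nominal schedule the whole of the primary contrast is app coaching since discharge against no scheduled counselling since discharge. It does not estimate app versus nutrition counselling received. The conclusion assumes that questionnaire and counselling share the visit and that no control contact occurs before day 30; the text supports both but does not guarantee them.

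The defect is one of labelling and permitted claim. The randomised comparison remains valid, and the 1-month sample-size arithmetic is unaffected. It matters because the synopsis and the body disagree on the primary time point. Resolving that in favour of 1 month as a mere typing correction, without changing the description of the comparator, would fix the mismatch in place.

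**What to change.** Reconcile the synopsis (Purpose) with sections 2(1) and 7(5), choosing the time point in light of the contrast it tests. There are two options.

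**(a) 3 months primary.** Make the STO22 eating-restriction score at 3 months the primary endpoint in all sections. Require the questionnaire to be completed before that day's counselling. Replace the 1-month assumptions in section 6(2) and the synopsis with a 3-month difference and SD, and recalculate. The form is already collected at 3 months, so no new data are needed. The cost is a new sample-size justification, which may not support the present 65 per group.

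**(b) 1 month primary.** State in sections 2(1) and 7(5) that the 1-month comparison tests early app coaching against no scheduled counselling after discharge. Require the questionnaire before the counselling session. State that no superiority over face-to-face counselling will be claimed from it. The cost is a narrower claim; the sample-size basis stays tied to the right time point.

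Both options leave the counselling schedule as it is and need one added instruction on the order of events at the visit.
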